### Technique

Technical aspects and application of the BYCROSS atherectomy system have been published previously [11, 12]. The BYCROSS™ has a coaxial, flexible, rotating shaft with an extendable tip and integrates an aspiration system for aspirating plaque debris and broken, as well as fallen thrombotic material. The expandable tip can increase the tip diameter from an outer diameter of 1.9 mm when closed to 4.7 mm when open. As the shaft rotates, the tip breaks the calcified atheroma or thrombus into small particles, which are simultaneously aspired into the guide sleeve and disposed of in the attached collection bag. Although BYCROSS is inserted via a guidewire, it does not require prior passage of an occlusion with the wire. Once the occluded segment is passed, the open-tip procedure is repeated on larger diameter vessels to further remove the remaining atheroma or thrombus. After passage of the lesion, regular angioplasty can be performed with or without a drug-eluting balloon.

### Adjuvant medical therapy

After the procedure, all patients receive aspirin 100 mg (1–0-0) and clopidogrel 75 mg (1–0-0) daily for at least 6 months. If there is something against this combination based on the patient-specific history (risk of falls, previous bleeding, use of oral anticoagulants such as Marcumar), individual adjustments will be made.

### Follow-up

All participants will be followed-up after successful intervention. Clinical assessments will be performed 90 days (± 14 days) and 12 months (± 2 weeks) after the procedure. The following assessments and/or procedures will be collected and reported for all subjects at follow-up visit.Stenosis assessment by Duplex UltrasoundAnkle-Brachial-Index (ABI) measurement, depending on the ABI a treadmill test orTranscutaneous oxygen partial pressure measurement (TcPO2)Rutherford classification [13]Target vessel revascularization (TVR)Target lesion revascularization (TLR)Measurement Quality of Live via EQ5D [15] questionnaireMeasurement of pain via numeric pain scale (NRS) [16]Minor or Major Amputation neededSerious adverse events recording. Each event will be assessed whether root-cause for the event is related to device, procedure or not related.

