### Study design

The study is designed as a multicenter (3 centers), prospective, single arm, observational study. The success of the procedure (primary endpoint) will be assessed in each participating subject, as well as safety outcomes (defined as freedom from serious adverse events associated with the device (SADE)). A total of 60 (target 20 each center) subjects with a symptomatic PAD will be enrolled in the study. After written informed consent, subjects will be continuously enrolled (registered). Subjects will be followed for a period of 12 months, including follow-up after, and follow-up 90 days after the procedure. The detailed study procedures are shown in the flowchart of study activities (Fig. 2).

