#### Study procedure

Schedule of events for this study are shown in Fig. 3. The study duration for each subject will be approximately 12 months, as follows:Screening of individuals who meet the inclusion criteriaProcedure with BYCROSS™ atherectomy systemFollow-up at 90 days after procedureFollow-up at 12 months after-procedure

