### Endpoints

The primary performance endpoint is technical success: Passage of the occlusion through the BYCROSS® device and residual stenosis after atherectomy of ≤ 50% compared to the reference diameter to allow angioplasty and/or stenting if needed, and complete procedural success with residual stenosis of ≤ 30%. The angiographic data will be examine at each study center by an independent radiologist or vascular surgeon with experience in interventional procedures. The primary safety endpoint is Freedom from device related Serious Adverse Events (SADEs) defined by the investigational site as part of normal reporting practices in any period between the procedure and 90 days after the procedure.

Secondary endpoints are listed in Table 2

**Table 2 Tab2:** Secondary endpoints, ^1^PACCS, peripheral arterial calcium scoring system

Secondary endpoints
a. target vessel revascularization (TVR) at 3 and 12 months
b. target lesion revascularization (TLR) at 3 and 12 months
c. The change of the Rutherford classification [13] at 3 and 12 months compared to pre-procedure
d. freedom from any minor or major amputation at 3 and 12 months
e. therapy success of the recanalization of the iliaco-femoro-popliteal vascular flow path depending on the access (crossover/antegrade/retrograde)
f. evaluation of the recanalization result of superficial femoralis artery (SFA) stenosis/occlusions using IVUS vs. angiography for the purpose of deciding on therapy for additional Angioplasty/stent implementation/Drug Eluting Balloon (DEB)
g. the evaluation of the recanalization result of BYCROSS use without primary wire passage
h. the evaluation of the recanalization result of stenoses/occlusions in combination with hybrid interventions
i. the evaluation of the correlation between calcification (measeared and calcified in accordance with PACCS^1 ^[14] and procedural complications

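### The follow-up section ties follow-up to a successful intervention, contradicting the all-subject follow-up stated elsewhere; applied literally, about 4 of 60 patients could miss the 90-day and 12-month visits

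*Protocol article*

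**What the plan says.** The Follow-up section of the protocol article opens with "All participants will be followed-up after successful intervention". Its next sentence times the visits from the procedure, not from success: "Clinical assessments will be performed 90 days (± 14 days) and 12 months (± 2 weeks) after the procedure". The list of assessments is then introduced as "collected and reported for all subjects at follow-up visit".

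Other sections set no success condition:

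- Study design: "Subjects will be followed for a period of 12 months". The primary endpoint of procedural success "will be assessed in each participating subject, as well as safety outcomes".
- Study procedure: "The study duration for each subject will be approximately 12 months".
- Endpoints: the primary safety endpoint counts device-related serious adverse events (SADEs) "in any period between the procedure and 90 days after the procedure".
- Safety: serious adverse events during the study must be documented, and the site reports them within 24 hours of learning of them. The same section has SAEs and SADEs recorded at each follow-up visit.

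Success has more than one meaning. The Abstract equates procedural success with passage of the occlusion. Endpoints requires passage plus residual stenosis of at most 50% for technical success, and at most 30% for complete procedural success. The Follow-up section does not say which of these it means.

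**The concern.** Success of the procedure is the primary performance outcome. A rule that starts follow-up only after success makes observation of every later outcome depend on that outcome. Patients in whom the device failed may do worse afterwards: the Background names distal embolism, vessel injury and perforation as risks of atherectomy, and Table 3 lists embolization and revision among the serious events. If these patients are not seen at 90 days and 12 months, target lesion and target vessel revascularization (TLR, TVR), Rutherford change and amputation are missing for them. SADEs that arise after discharge come to light only if the site happens to hear of them. The study has one arm, so no comparator would reveal a selective loss. Because the key word is undefined, the three centers could also draw the line in three different places.

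**Working it through.** **Reading the sections together.** Only one sentence contains the success condition. Study design, Study procedure, Endpoints and the assessment list in Follow-up all refer to subjects without it. No section withdraws, excludes or replaces patients after device failure. The text therefore contradicts itself on who is followed, and the balance favours everyone.

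**Inputs from the document.** Planned N = 60, i.e. 3 centers × 20 (Study design). Earlier investigation: 39 of 42 met the acute success criterion, and all patients were free of serious device-related events at 30 days (Discussion).

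**The document's own figure.** 39/42 = 92.9%, which agrees with the stated success rate of over 92%. The failure share is f = 3/42 = 7.1%, exact (Clopper-Pearson) 95% interval 1.5% to 19.5%.

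**Patients affected on the literal reading.**

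- Expected failures: 60 × 3/42 = 4.3, leaving about 56 followed.
- Range: 60 × 0.015 = 0.9 to 60 × 0.195 = 11.7, so roughly 1 to 12.
- Chance of at least one failure: 1 − (39/42)^60 = 98.8%.

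**Effect on freedom from SADE.** Let p_s and p_f be the 90-day SADE risks in successes and failures. Among all treated patients, freedom is 1 − [(1 − f)·p_s + f·p_f]; among successes alone it is 1 − p_s. The overstatement is f·(p_f − p_s). The document gives neither risk, so the values below are assumptions.

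| p_s | p_f | All treated | Successes only | Overstatement (points) |
|---|---|---|---|---|
| 2% | 2% | 98.0% | 98.0% | 0 |
| 2% | 10% | 97.4% | 98.0% | 0.6 |
| 2% | 25% | 96.4% | 98.0% | 1.6 |
| 2% | 50% | 94.6% | 98.0% | 3.4 |
| 0% | 100% | 92.9% | 100% | 7.1 |

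The last row is the ceiling at f = 3/42. With four whole patients it is 4/60 = 6.7 points. The overstatement is proportional to f, so it moves with the failure share over its interval of 1.5% to 19.5%. The table also assumes that every SADE in a failed case goes uncounted. The Safety section makes that too pessimistic, because events known to the investigator must be reported.

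**What the earlier safety result adds.** If its statement about all patients includes the three failures, 0 of 3 had an event at 30 days. The exact upper 95% limit is 1 − 0.025^(1/3) = 70.8%, so it does not rule out any assumed p_f up to 50%. It also covers neither 90 days nor the 12-month outcomes.

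**The case against.** The strongest reply is that this is loose wording for follow-up after the intervention. The sentence has all participants as its subject, the visits are timed from the procedure, and the assessments are for all subjects. The figures with the activity flow chart and participant flow are not visible here, and the article condenses a full protocol; either could settle who is followed. This reply has force. It argues for removing the word, since on that reading it does no work.

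A reader might go further and infer that failed cases drop out of the 90-day safety endpoint and of all later endpoints by design. The documents do not support that. No section removes such patients from a denominator, and Study design assesses success and safety in every participant. The safety window opens at the procedure, and the reporting duty applies whatever the procedural result. Perforation, embolization or conversion during the procedure would be known to the site and counted.

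Two further objections stand: the event rates in failures are assumed, and the only safety result the document offers for failures is favourable, though very small.

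What the objection does not remove is the exposure after discharge. SAE and SADE recording is also tied to follow-up visits, and TLR, TVR, Rutherford class and amputation are collected there. The 24-hour reporting duty does not replace those visits.

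**Conclusion.** The point holds as an internal contradiction that carries a risk of outcome-dependent loss. It is not a demonstrated exclusion or a demonstrated bias. On the literal reading about 4 of 60 patients (roughly 1 to 12) could miss both visits. This assumes that the earlier failure share of 3/42 carries over and that success means something close to the earlier acute criterion. If it means the 30% residual-stenosis criterion, more could be affected, but the document gives no rate for that.

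The overstatement of freedom from SADE is about 0.6 to 3.4 points under the assumed rates, zero if failures and successes have equal risk, and about 7 points at most at a 3/42 failure share. The actual effect on the safety endpoint should be smaller, because events known to the site are still reported. The greater exposure is in late SADEs unknown to the site and in the revascularization, Rutherford and amputation outcomes at 3 and 12 months. Its direction, in the device's favour, is plausible but not shown by the document.

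**What to change.** Reconcile the sections by replacing the opening sentence of Follow-up with: *All subjects in whom use of the BYCROSS was attempted are followed at 90 days and 12 months regardless of procedural success.* Use that set as the denominator for the primary safety endpoint and for the 3- and 12-month endpoints. Recruitment has been open since August 2022, so ask the three centers whether any failed cases were not followed, and retrieve their 90-day and 12-month status from records.

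The cost is a one-sentence amendment and visits or record retrieval for a few patients, about four on the figures above. The safety result may become slightly less favourable. Retrieval cannot fully replace a missed visit, so the clarification should reach the sites soon.

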### Safety

Serious adverse events (SAEs) occurring during the conduct of this study must be documented. The list of potential SAEs is provided in Table 3. All SAEs and serious adverse device events (SADEs) associated with the device will be recorded at each follow-up visit. Reporting will be in accordance with local requirements and policies. If the investigator identifies an SAE/SADE, an SAE reporting form must be completed and faxed or emailed to Taryag Medical (TARYAG-MEDICAL GmbH, Israel, [contact]) within 24 h of the investigator’s knowledge of the event.

**Table 3 Tab3:** List of serious adverse events

Serious adverse events
a death
b serious deterioration in the health of the subject, that resulted in any of the following:
(I) life-threatening illness or injury,
(II) permanent impairment of a body structure or a body function,
(III) hospitalization or prolongation of patient hospitalization,
(IV) medical or surgical intervention to prevent life-threatening illness or injury or permanent impairment to a body structure or a body function,
(V) chronic disease
c Acute limb ischemia as a result of the procedure e.g. peripheral embolization
d Necessary thrombectomy/revision as a result of the procedure (surgical or interventional)
e Unplanned major amputation, above or below the knee

## Discussion

This study is designed as a multicenter, prospective, single arm, observational study to evaluate the success of the procedure and safety outcomes. A total of 60 (target 20 each center) individuals with a symptomatic PAD will be enrolled in the study.

The novel BYCROSS™ atherectomy represents a further development of existing atherectomy systems. During development, several limitations of other systems were identified and eliminated. The device does not require special guide wires and introducer sheaths, it is not necessary to first pass the occlusion with a guide wire. It operates without major equipment, pedal or nonsterile devices, and it is battery powered [17].

The safety and efficacy of the BYCROSS™ device was successfully tested in the Taryag Medical Clinical Investigation “BYCROSS™ Study” 2018/2019 (CIV-17–10-021851). Based on the BYCROSS trial and clinical experience, the BYCROSS device was shown to provide a solution with potentially minimal complications and improved treatment outcomes compared to simple balloon angioplasty (POBA) or stent-assisted POBA, especially in severely calcified vessels.

The procedural protocols of the clinical investigation demonstrated that the BYCROSS is a safe and effective option for intraluminal revascularization by avoiding vessel wall damage. Furthermore, no physical and mechanical changes of the BYCROSS were observed after the procedure at any PACCS [14] score or lesion length (up to 420 mm).

In the clinical investigation 42 patients with chronic limb ischemia and target vessel stenosis ≥ 80% with total or subtotal occlusion were enrolled and underwent procedure using the BYCROSS™ atherectomy device and adjunctive therapy, such as balloon and/or stenting if required.

Success of the acute intervention as the primary performance endpoint was assessed in each participating subject immediately after the intervention, and the primary safety endpoint was assessed after 30 days. Subjects were followed up over a 6-month period for assessment of the secondary safety endpoint and secondary performance endpoints. Thirty-nine of the 42 patients (in the full analysis (FA)) met the acute treatment success criterion. All patients were free of serious (major) device-related adverse events (MDAE) 30 days after the procedure. In conclusion, no serious device-related adverse events occurred in the clinical trial. The success rate of the acute intervention was over 92%.

## Conclusion

The purpose of this prospective national multicenter observational study is to collect further clinical data on the safety and performance of the BYCROSS atherectomy system and to monitor short- and mid-term treatment success.

The BYCROSS atherectomy system may be a novel device for the minimally invasive treatment of longstanding calcified lesions previously reserved for bypass surgery.

## Trial status

The trial has been registered in the German Clinical Trials Register (DRKS00029947), on 19 September 2022.The full WHO trial registration dataset is available via https://trialsearch.who.int/Trial2.aspx?TrialID=DRKS00029947. The protocol version is 2022–01; 20 May 2022, Recruitment began on 11 August 2022. The expected date for recruitment completion is December 2023.

## Data Availability

After publication of the study results, a fully anonymised data set and the statistical code can be made available upon justified scientific request and after ethical approval has been granted. Depending on the extent of the data use and the planned research, either appropriate credit or co-authorship must be granted to the authors of this study. A sample of the CRF used for this study can be provided upon justified scientific request.
